### Implementation {16c}

The randomization sequence will be implemented using sequentially numbered, opaque, sealed envelopes (SNOSE) containing group assignments (esketamine 0.25 mg/kg or saline placebo). These envelopes will be securely stored in a locked cabinet, accessible only to an unblinded anesthesia nurse (not involved in outcome assessment).

## Assignment of interventions: blinding

### Who will be blinded {17a}

This study will be conducted in a double-blind manner where the patients, endoscopists, anesthesiologists responsible for intraoperative care, and outcome assessors will all be blinded to the group assignment.

All study drugs will be prepared by an independent anesthesiologist who is not involved in the subsequent anesthesia management, data collection, or outcome assessment. This anesthesiologist will have access to the randomization schedule.

Both the esketamine and the placebo (0.9% normal saline) will be drawn up to identical volumes of 10 mL in identical 20-mL sterile syringes. The syringes will be wrapped in opaque foil to prevent any visual distinction between the two solutions. The wrapped syringes will be labeled only with the patient’s study identification number.

The prepared, blinded syringe will be handed to the procedural anesthesiologist immediately before the initiation of anesthesia. This anesthesiologist will administer the study drug as a bolus without knowing its content.

### Procedure for unblinding if needed {17b}

Emergency unblinding is permitted only for suspected serious adverse reactions (SAEs). The principal investigator (PI) will hold the randomization list and be responsible for unblinding if necessary. All such events will be documented within 24 h to the IRB. Sealed envelopes attached to CRFs will reveal allocation.

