## Assignment of interventions: allocation

### Sequence generation {16a}

The allocation sequence will be computer-generated by an independent biostatistician using stratified block randomization (SAS 9.4). Stratification will be based on two clinically relevant factors: age group (18–65 years vs. > 65 years) and OSA severity (STOP-Bang score 5–6 vs. ≥ 7). Variable block sizes (4, 6, 8) will be used to enhance unpredictability, with details stored in a password-protected file accessible only to the trial statistician and DSMB chair. This ensures allocation concealment and prevents selection bias.

Roles are strictly separated to maintain blinding and prevent bias: sequence generated by an independent biostatistician, enrollment and consent completed by GCP-certified investigator, and intervention assigned by unblinded anesthesia nurse for prepares and dispenses study drugs per SNOSE system. The structured approach aligns with CONSORT and SPIRIT guidelines, ensuring robust randomization and minimizing bias.

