### Concealment mechanism {16b}

The complete randomization scheme (including block sizes) will remain concealed in a restricted-access file. Emergency unblinding materials (sealed envelopes) will be attached to each participant’s CRF, accessible only to the chief anesthesiologist in case of serious adverse events.

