## Statistical methods

### Statistical methods for primary and secondary outcomes {20a}

All analyses will be conducted using SPSS 23.0 (IBM Corp) by a statistician blinded to group allocation. The primary outcome will be analyzed using a one-sided *Z*-test at *α* = 0.025, while secondary outcomes will employ two-sided tests with *α* = 0.05.

Continuous variables will be assessed using the Kolmogorov–Smirnov test examining for normality. Normally distributed data will be presented as mean ± standard deviation (SD). Non-normal data will be presented as median or interquartile range (IQR). Categorical variables will be presented as counts and percentages.

For the primary outcome of hypoxemia incidence, we will employ a one-sided Z-test for proportions to evaluate the hypothesized reduction in the esketamine group, reporting absolute risk differences with 95% confidence intervals. Secondary outcomes will be analyzed using appropriate statistical tests based on variable characteristics: continuous normally distributed variables will be compared using independent *t*-tests, while non-normal continuous data will be assessed with Mann–Whitney *U* tests. Categorical outcomes will be analyzed using *χ*^2^ tests or Fisher’s exact tests as warranted by sample sizes. For time-to-event outcomes such as duration of hypoxemic episodes, we will utilize Kaplan–Meier survival analysis with log-rank tests. Longitudinal physiological measurements including mean arterial pressure and heart rate will be evaluated using repeated measures ANOVA, with post hoc Bonferroni corrections applied to account for multiple comparisons while maintaining the overall type I error rate at *α* = 0.05. All comparative analyses will be conducted by a blinded statistician using SPSS version 23.0, with two-sided tests (*α* = 0.05) employed for all secondary outcomes to conservatively assess potential group differences.

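### The protocol contradicts itself on who holds the randomisation sequence and who unblinds, and it gives the list to a principal investigator who is not excluded from enrolment

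*Protocol article*

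**What the plan says.** Five neighbouring sections of the protocol article deal with access to allocation information.

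- **Sequence generation {16a}.** An independent biostatistician generates the sequence, "with details stored in a password-protected file accessible only to the trial statistician and DSMB chair". The section then asserts that this secures concealment and prevents selection bias. It assigns enrolment and consent to a GCP-certified investigator, and preparation and dispensing of study drug to an unblinded anesthesia nurse using sealed envelopes.
- **Concealment mechanism {16b}.** "The complete randomization scheme (including block sizes) will remain concealed in a restricted-access file". Emergency envelopes are attached to each CRF and are "accessible only to the chief anesthesiologist in case of serious adverse events".
- **Implementation {16c}.** The allocation envelopes are in a locked cabinet, "accessible only to an unblinded anesthesia nurse (not involved in outcome assessment").
- **Who will be blinded {17a}.** An independent anesthesiologist prepares all study drugs. "This anesthesiologist will have access to the randomization schedule".
- **Procedure for unblinding if needed {17b}.** "The principal investigator (PI) will hold the randomization list and be responsible for unblinding if necessary". The section ends by saying that the envelopes attached to the CRFs disclose the allocation.

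**The concern.** Allocation concealment depends on whoever decides to enrol a patient not knowing the next assignment. The protocol bases its assurance on a short, closed list of people with access, then widens that list in two later sections. One of the added people is the PI. A PI ordinarily has authority over recruitment, and nothing in this document removes the PI from it.

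Someone who both holds the list and enrols could bring forward, defer or decline a patient according to the coming assignment. The arms could then differ in hypoxemia risk before any drug is given, and the comparison of hypoxemia incidence would no longer rest on randomisation alone.

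There is also a practical problem. Site staff cannot follow all five sections at once, because they name different people for the same task.

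**Working it through.** The point depends on no figure, so there is nothing to recompute. The check is to set the statements side by side, task by task.

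| Task | One section | Another section | Compatible? |
|---|---|---|---|
| Access to the sequence | {16a}: trial statistician and DSMB chair only | {17a}: drug-preparing anesthesiologist; {17b}: PI | No |
| Preparing study drug | {16a}, {16c}: unblinded nurse, from envelopes only the nurse can reach | {17a}: independent anesthesiologist, with the schedule | No |
| Emergency unblinding | {16b}: envelopes for the chief anesthesiologist only | {17b}: PI, who also holds the list | No |

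**Access.** {16a} names two roles and says only these two. {17a} adds one and {17b} adds one, so 2 + 1 + 1 = 4 roles have access against the two declared exclusive.

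**Can the PI enrol?** Enrolment and consent go to a GCP-certified investigator ({16a}, {26a}). That description does not exclude the PI. The statement in {16a} that roles are separated covers the sequence generator, the enroller and the nurse, and does not mention the PI. {17a} lists who is blinded, and the PI is not on the list. Study setting {9} confirms a single centre, so there is no other site at which recruitment would be beyond a list-holder's reach.

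**Do the block sizes help?** Blocks of 4, 6 and 8 make the next assignment hard to guess from past ones. They give no protection against someone who can read the next assignment.

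**Is PI custody needed?** The only purpose {17b} gives for it is unblinding. The same section says the sealed envelopes reveal allocation. A single-patient envelope answers the emergency question without exposing any future assignment, so the list adds exposure and no function.

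**Where the envelopes are kept.** {16b} and {17b} attach the code-break envelopes to the CRFs. Plans for assessment and collection of outcomes {18a} has blinded assessors record outcomes on those CRFs. Each patient's allocation therefore sits, sealed, with the people who must not know it.

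**The case against.** The strongest reply is that the protocol has several real safeguards: sealed envelopes in a locked cabinet, identical foil-wrapped syringes labelled by study number, a preparer kept out of anesthesia management, data collection and outcome assessment, and blinded assessors. These stand. They protect the treating and assessing stages well, and they narrow the exposure to enrolment by someone who holds the list.

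It can also be said that the file in {16a} might contain only generation details such as block sizes, and that {17b} does not say the PI's list is complete. Both are possible. Even so, {16b} places the complete scheme under restricted access without mentioning the PI, and {17b} puts no limit on the list. The conflicts over the preparer and over unblinding do not depend on this reading.

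Three stronger readings are tempting and are not supported.

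- A reader might infer that the PI is free to treat or assess patients while knowing allocation. {17a} requires endoscopists, treating anesthesiologists and outcome assessors to be blinded, and {18a} repeats this for assessors. A list-holder could fill those roles only by breaching the protocol.
- A reader might infer that the trial statistician's file access contradicts the promise in Statistical methods {20a} that analyses are done "by a statistician blinded to group allocation". The document never says these are the same person. Interim analyses {21b} adds an independent statistician who unblinds. Different people can satisfy all three sections.
- A reader might use the 26–85% range in the Discussion as a gap between low-risk and high-risk patients to size the bias. That range is hypoxemia incidence reported across cited sources. It is not a gradient within this trial's population.

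**Conclusion.** The contradiction is certain on the text: the access rule in {16a} cannot hold alongside {17a} and {17b}, and drug preparation and emergency unblinding are each assigned to two different roles. Concealment is therefore not assured against a PI who holds the list.

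This conclusion rests on two readings. The first is that the list in {17b} covers future allocations, which is the natural sense of the words. The second is that the PI may take part in enrolment or consent, which the protocol neither states nor rules out.

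A reader might conclude that concealment has already failed. Nothing in the document shows that. It is an unmitigated risk, confined mainly to enrolment, and its effect on the primary result cannot be estimated from what is given. It deserves correction because the exposure serves no purpose that the envelopes do not already serve.

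**What to change.** 1. In {17b}, delete PI custody of the list. Keep it only with the holders named in {16a}, and state that none of them enrols, treats, assesses or carries out the blinded analysis.
2. Reconcile {16a}, {16c} and {17a} to one unblinded preparer, who opens only the next envelope in sequence and has no access to the full schedule.
3. Reconcile {16b} and {17b} to one named role for emergency unblinding. The choice of role is the sponsor's. That role uses only the existing single-patient sealed envelopes, stored apart from the CRFs that blinded assessors complete.
4. Enrolment began on April 1, 2025 and is planned to run to December 31, 2026, so rewording alone does not cover past access. Document who has had access to the list so far, and state that anyone who has had it takes no part in enrolment.

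The cost is small: edits to these sections, relocation of one file and the envelopes, and a short access record. The roles already exist. If the PI has been enrolling while holding the list, another investigator must take over enrolment. The change may need ethics review under {11b} and {25} if it counts as a change to safety procedures or risks.

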## Data collection and management

### Plans for assessment and collection of outcomes {18a}

All outcomes will be systematically assessed, collected, and recorded on CRFs by blinded assessors across three phases: baseline demographics (age, sex, BMI), clinical characteristics (ASA status, STOP-Bang score, Difficulty in mask ventilation [DMV] risk factors), and room-air SpO_2_ will be collected pre-procedure; continuous vital signs (HR/SpO₂/NBP recorded every 30 s), propofol requirements, hypoxemia episodes (SpO_2_ < 90% > 10 s), procedure/recovery times, and adverse events (graded by blinded assessors) collected intraprocedure; Satisfaction (10-cm VAS), PACU recovery metrics (MOAA/S = 5 time), and AEs (graded 1–3 for severity/causality) collected post-procedure.

### Plans to promote participant retention and complete follow-up {18b}

To ensure high retention rates and complete follow-up data collection, the following strategies will be implemented: (1) clear consent discussions with visual aids emphasize study importance; (2) fixed anesthesia team and real-time CRF completion minimize errors; (3) immediate PACU assessments precede discharge, with small compensation (meal vouchers) offered. Withdrawals are documented without care penalties, and all collected data are retained for ITT analysis. Quarterly DSMB reviews monitor retention rates, with protocol deviations logged for sensitivity analyses. All data will be recorded in CRFs. Missing data (< 5%) will use mean imputation, analyzed via both ITT and per-protocol approaches. CRFs are publicly accessible via trial registry (ChiCTR2500099420).

### Data management {19}

Data will be collected electronically using a password-protected system with built-in range checks and mandatory fields. Data will be entered into Research Electronic Data Capture (REDCap) with range checks by blinded staff, with 10% double-entry verification. Standardized coding will ensure consistency. The system features role-based access, two-factor authentication, and encryption. All data will be stored for 10 years post-study on secure, backed-up servers.

### Confidentiality {27}

All participant data will be handled with strict confidentiality measures, collected by designated anesthesiologists and follow-up physicians, immediately recorded in password-protected electronic CRFs. Original records (medical charts, consent forms, CRFs) stored securely for 10 years. Electronic data are encrypted and accessible only to study statisticians. De-identified data could be shared with DSMB for monitoring, with no public release until trial completion and publication. Physical documents are shredded after 10 years per hospital policy, and electronic archives are permanently deleted.

### Plans for collection, laboratory evaluation and storage of biological specimens for genetic or molecular analysis in this trial/future use {33}

Not applicable. No laboratory evaluation and storage of biological specimens for genetic or molecular analysis in this trial.

## Statistical methods

### Statistical methods for primary and secondary outcomes {20a}

All analyses will be conducted using SPSS 23.0 (IBM Corp) by a statistician blinded to group allocation. The primary outcome will be analyzed using a one-sided *Z*-test at *α* = 0.025, while secondary outcomes will employ two-sided tests with *α* = 0.05.

Continuous variables will be assessed using the Kolmogorov–Smirnov test examining for normality. Normally distributed data will be presented as mean ± standard deviation (SD). Non-normal data will be presented as median or interquartile range (IQR). Categorical variables will be presented as counts and percentages.

For the primary outcome of hypoxemia incidence, we will employ a one-sided Z-test for proportions to evaluate the hypothesized reduction in the esketamine group, reporting absolute risk differences with 95% confidence intervals. Secondary outcomes will be analyzed using appropriate statistical tests based on variable characteristics: continuous normally distributed variables will be compared using independent *t*-tests, while non-normal continuous data will be assessed with Mann–Whitney *U* tests. Categorical outcomes will be analyzed using *χ*^2^ tests or Fisher’s exact tests as warranted by sample sizes. For time-to-event outcomes such as duration of hypoxemic episodes, we will utilize Kaplan–Meier survival analysis with log-rank tests. Longitudinal physiological measurements including mean arterial pressure and heart rate will be evaluated using repeated measures ANOVA, with post hoc Bonferroni corrections applied to account for multiple comparisons while maintaining the overall type I error rate at *α* = 0.05. All comparative analyses will be conducted by a blinded statistician using SPSS version 23.0, with two-sided tests (*α* = 0.05) employed for all secondary outcomes to conservatively assess potential group differences.

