##### Trial design {8}

This single-center, prospective, double-blind, randomized, superiority trial will evaluate whether low-dose esketamine (0.25 mg/kg) reduces hypoxemia incidence compared to placebo during propofol-sedated gastroscopy in patients with moderate-to-high OSA risk (STOP-Bang score ≥ 3).We will enroll 294 participants, randomly allocating them in a 1:1 ratio to either Esketamine group (0.25 mg/kg esketamine + propofol) or Control group (equal-volume saline + propofol). The study duration is 21 months. Eligible patients will be screened according to inclusion/exclusion criteria, with baseline characteristics recorded in case report forms (CRFs). Continuous monitoring of vital signs will occur from gastroscopy room admission through Post-Anesthesia Care Unit (PACU) recovery, with all interventions and assessments standardized (Fig. 1).

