### Outcomes and definitions {12}

Primary outcome is the hypoxemia incidence, defined as SpO_2_ < 90% for > 10 consecutive seconds during the procedure [18]. Timing begins at first SpO_2_ reading < 90% and continues until resolution.

Secondary outcomes are as follows:Severe hypoxemia incidence, defined as SpO₂ ≤ 75% for any duration or SpO₂ ≤ 90% for ≥ 60 consecutive seconds or longer during the procedure [17].Hypoxemia duration, defined as total cumulative time (seconds, mean [SD]/median [IQR]) with SpO₂ < 90% during procedure.Emergency airway intervention, defined as requiring jaw thrust maneuver, mask-assisted ventilation with procedure interruption, tracheal intubation during procedure and in PACU.Hypotension incidence defined as MAP decrease ≥ 20% compared with baseline (average of 3 pre-procedure readings) during procedure and in PACU.Involuntary body movements are defined as any limb/trunk movements requiring physical restraint or procedure interruption during the procedure.Total propofol dose defined as cumulative amount (mg, mean [SD]/median [IQR]) administered during procedure.Length of procedure (minutes, mean [SD]/median [IQR]) defined as the time quantum from gastroscope insertion to complete withdrawal.Recovery time (minutes, mean [SD]/median [IQR]) defined as the time quantum from scope removal to achieving MOAA/S score of 5 or responsive to normal voice.Clinician satisfaction measured via 10-cm VAS immediately post-procedure (0 = extremely dissatisfied, 10 = completely satisfied) after the procedure.AEs will be documented and assessed continuously during the procedure and in the PACU. Occurrence counts and severity (where applicable) will be documented in the CRFs as follows:Cough: Defined as ≥2 consecutive coughs during the procedure or in the PACU; assessed by direct observation and recorded as presence/absence.Hiccups: Defined as ≥2 episodes within 1 minute; recorded as presence/absence during the procedure or in the PACU.Nausea/vomiting: Graded on a 3-point severity scale (1=mild/nausea only, 2=moderate/transient vomiting, 3=severe/prolonged vomiting) and assessed both during the procedure and in the PACU.Reflux/aspiration: Defined as visible gastric content in the oropharynx or airway; recorded as presence/absence during the procedure.Laryngospasm: Defined as complete airway obstruction with no airflow despite respiratory effort; assessed by auscultation and waveform capnography, and recorded as presence/absence during the procedure.

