### Sample size {14}

All calculations were performed using PASS 15.0 (NCSS, LLC), with parameters verified by an independent statistician. The sample size calculation was based on detecting a clinically meaningful difference in the primary outcome of hypoxemia incidence (SpO_2_ < 90% for > 10 s) between study groups. From our pilot data, we anticipate a 50% incidence of hypoxemia in the control group receiving standard propofol sedation. We hypothesize that low-dose esketamine will achieve an absolute risk reduction of 15%, corresponding to a 35% hypoxemia incidence in the intervention group. Using a one-tailed *Z*-test for proportions (unpooled) with 80% power (*β* = 0.20) and a significance level of *α* = 0.025 (selected because esketamine’s established respiratory safety profile makes increased hypoxemia biologically implausible; detecting non-inferiority/superiority is the sole clinical priority.), we calculated a minimum requirement of 132 participants per group. To account for potential 10% attrition, we will enroll 147 participants per group (*N* = 294 total). This conservative approach ensures adequate power even if the actual control group incidence varies between 45 and 55% or if dropout rates reach 15%. The one-tailed design is appropriate given esketamine's established respiratory safety profile and the clinical irrelevance of detecting increased hypoxemia risk with this intervention.

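### Nausea/vomiting is graded on an ordered scale, but the only tests named for categorical outcomes ignore order: a minor point, cheap to improve

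*Protocol article*

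**What the plan says.** Protocol article, Outcomes and definitions {12}: nausea/vomiting is listed among the adverse events and is "Graded on a 3-point severity scale (1=mild/nausea only, 2=moderate/transient vomiting, 3=severe/prolonged vomiting"). It is assessed both during the procedure and in the PACU. The other events in that list (cough, hiccups, reflux/aspiration, laryngospasm) are recorded as present or absent. The same section says that occurrence counts and, where applicable, severity are documented in the CRFs.

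Statistical methods {20a}: "Categorical outcomes will be analyzed using *χ*^2^ tests or Fisher’s exact tests as warranted by sample sizes". The only rank test is tied to another data type: "non-normal continuous data will be assessed with Mann–Whitney *U* tests". On level and sidedness, "secondary outcomes will employ two-sided tests with *α* = 0.05". The section also promises tests suited to the characteristics of each variable. Section {20b} states that there are no additional analyses.

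No section says whether nausea/vomiting is compared across grades or as any versus none. No rate, grade distribution, effect size or power target is given for it.

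**The concern.** An ordered scale has been assigned to a family of tests that treats its levels as unlabelled boxes. A Pearson χ² or Fisher test on the graded table returns the same p-value if the grades are shuffled. It spreads its sensitivity over every possible pattern of difference, including many that nobody expects. If esketamine makes nausea/vomiting uniformly worse, or uniformly milder, such a test is more likely to miss it than one that uses the order. Collapsing to any versus none avoids that loss, but then a move from nausea to prolonged vomiting at equal incidence cannot be seen. At stake is part of the tolerability comparison, not the primary result.

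**Working it through.** **Inputs from the protocol.** Allocation: "randomly allocating them in a 1:1 ratio". Sample size: "we calculated a minimum requirement of 132 participants per group"; "To account for potential 10% attrition", "we will enroll 147 participants per group". The inflation reproduces: 132/(1 − 0.10) = 146.7, rounded up to 147. Test level: two-sided 0.05. The protocol states no power figure for nausea/vomiting, so there is none to reproduce.

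**Assumed inputs (not in the protocol).** Control percentages for none/1/2/3 of 90/6/3/1, 80/12/6/2 and 70/18/9/3, and a common odds ratio (OR) of 1.5 or 2 towards worse grades with esketamine.

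**Shift formula.** For each cut k, odds of grade ≥ k under esketamine = OR × odds of grade ≥ k under control. Example, 80/12/6/2 with OR 2:
- any: 0.20/0.80 = 0.25, doubled to 0.50, giving 0.50/1.50 = 33.3%
- grade ≥ 2: 0.08/0.92 = 0.0870, doubled to 0.1739, giving 14.8%
- grade 3: 0.02/0.98 = 0.0204, doubled to 0.0408, giving 3.9%

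The esketamine distribution is therefore 66.7/18.5/10.9/3.9%.

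**Simulated power (%), 147 per arm, 20,000 trials per row.** M–W is the tie-corrected Mann–Whitney test; trend is the linear test on scores 0–3. Differences are taken before rounding.

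| Control none | OR | 2×4 χ² | M–W | M–W minus 2×4 | Trend | Any-vs-none χ² | M–W minus any |
|---|---|---|---|---|---|---|---|
| 90% | 1.5 | 11.7 | 20.4 | 8.7 | 17.9 | 20.6 | −0.2 |
| 90% | 2 | 34.8 | 52.7 | 17.9 | 47.5 | 53.0 | −0.3 |
| 80% | 1.5 | 19.7 | 30.7 | 11.0 | 28.1 | 30.2 | 0.5 |
| 80% | 2 | 57.6 | 74.5 | 16.9 | 70.0 | 73.5 | 1.0 |
| 70% | 1.5 | 25.3 | 39.2 | 13.8 | 36.4 | 38.1 | 1.1 |
| 70% | 2 | 69.1 | 84.2 | 15.1 | 80.8 | 81.8 | 2.4 |

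A further control distribution, 85/9/4/2 (4,000 trials per setting), gives 16.4 vs 26.6 at OR 1.5 and 49.1 vs 67.6 at OR 2, gaps of 10.2 and 18.5 points. With no effect, Mann–Whitney rejects in 4.9–5.1% of trials in the three tabulated settings. The trend test gains less than Mann–Whitney over the 2×4 table, about 6–13 points.

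At 132 per arm the picture is the same. With 70% none and OR 2: 63.8 (2×4), 79.9 (M–W), 77.6 (any vs none).

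**Analytic cross-check.** Find the noncentrality λ at which a 1-df χ² test (critical value 3.841) has a given power, then apply the same λ to 3 df (critical value 7.815). For 70% power, λ ≈ (1.96 + 0.524)² = 6.17, and the 3-df power is 53.1%, a loss of 16.9 points. At 50% and 80% the loss is 15.5 points each. This agrees with the simulation and shows that the gap comes mainly from the extra degrees of freedom. That is also why any versus none, with 1 df, keeps nearly all the power.

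**Where the order hurts.** Under assumed patterns that are not a uniform shift, the 2×4 χ² wins. With nausea up and vomiting down it has 71% power against 6% (132 per arm); with only the severe grade reduced, 59% against 20%. These sizes depend on the patterns chosen. They show that the reversal can be large, not how likely it is.

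Fisher's exact test on the full table was not simulated. It ignores order in the same way.

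**The case against.** The strongest reply is that the protocol never specifies a 2×4 table. Counting patients with any nausea/vomiting, testing that with χ² or Fisher, and tabulating the grades fits the text equally well. On that reading the loss is at most about 2.5 points in the settings above. This stands, and it is why the power figure can only be conditional. It does not remove the point, because under that reading the severity grades enter no stated comparison.

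Second, χ² and Fisher are valid, need no common-shift assumption and are better for some effects. This also stands. The scale joins two symptoms (grade 1 is nausea alone; grades 2 and 3 are vomiting), so a uniform shift is itself an assumption. A reader might infer that the named tests are an error with nothing to recommend them; the figures above contradict that.

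Third, the protocol nowhere says that severity was graded in order to compare it between arms. Section {12} speaks of documenting it, and {22} links severity grading of sedation-related events to CRF recording and ethics reporting. Nor is direction lost altogether, since counts and percentages by arm will show it.

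Fourth, this could be called a detail for a fuller plan. But {20a} does assign a test family to categorical outcomes, and that family does not fit this variable well.

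**Conclusion.** The point holds as a minor improvement, not as an error. The scale is ordered and no stated test uses the order.

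A reader might infer that this trial loses 8–18 points of power on nausea/vomiting. The protocol does not support that as a fact. The range requires all of the following: grades compared as a 2×4 table, 147 per arm, control rates of 10–30%, a proportional-odds shift of 1.5–2, and Mann–Whitney as the comparator. The table is one possible reading, and the rates and effects are assumptions. Over a wider assumed grid (control rates 5–50%, OR 0.33–3, 132 or 147 per arm) the gap runs from 0.4 to 21.7 points. With any versus none it is about 0–2.5 points at control rates of 10–30%, and severity is left out.

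The outcome is one adverse event with no power target, and the primary analysis is unaffected.

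**What to change.** In {20a}, add that the worst nausea/vomiting grade per patient (0 = none, 1, 2, 3, over procedure and PACU) is compared between arms with one pre-chosen ordinal test: tie-corrected Mann–Whitney, or a linear-by-linear trend test. Tabulate counts and percentages by grade and arm. Report a proportional-odds ratio with 95% CI only if the severe cells are not too sparse; at the assumed 1–3% severe, the control arm would hold about 1.5–4.4 such patients (0.01 × 147 to 0.03 × 147). Keep χ²/Fisher for the presence/absence events.

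The cost is one sentence, with no new data and standard software. It should be settled before anyone deciding on the analysis has seen results by arm, which means before the planned midpoint unblinding in {21b}. The real downside is lower sensitivity to differences that do not run in one direction, such as more nausea but less vomiting. That loss can be substantial, so the tabulated grades must be read alongside the test.
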